# The effect of different flushing and locking techniques on catheter occlusion rates in central venous catheters: protocol for a multicentre, randomized controlled, parallel-group, open-label, superiority clinical trial

**DOI:** 10.1186/s13063-024-08141-6

**Published:** 2024-06-12

**Keywords:** Central venous catheter, Intermittent flushing, Continuous infusion, KVO, Catheter patency

## Abstract

**Background:**

Maintaining venous access is of great clinical importance. Running a slow continuous infusion to keep the vein open (KVO) is often used in peripheral intravenous catheters (PIVCs). Previous studies have compared the effects of intermittent flushing and continuous infusion via peripherally inserted central catheters (PICCs). In this study, we applied KVO to central venous catheters (CVCs) and compared the occlusion rate of this technique with that of the intermittent flushing technique.

**Method:**

This is a randomized controlled trial of 14 hospitals in China. A total of 250 patients will be recruited in this study, and they will be randomized at a 1:1 ratio. After study inclusion, patients who will undergo CVC insertion will receive intermittent flushing with prefilled saline syringes (control group) or KVO infusion with elastic pumps (test group). All the catheters will be checked for patency by scoping Catheter Injection and Aspiration (CINAS) Classification on Days 3 and 7. The primary outcome is the rate of catheter occlusion in 7 days. Patients will be followed up until 9 days after CVC insertion, catheter occlusion, or catheter removal. The secondary outcomes are the rate of catheter occlusion in 3 days, nurse satisfaction, cost-effectiveness, adverse event rate, catheter-related bloodstream infection rate, catheter-related thrombosis rate, extravasation rate, phlebitis rate, and catheter migration.

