In the control group, prefilled saline syringes containing 10 ml of 0.9% sodium chloride injection will be used to flush and lock the catheter via pulsatile flushing and the positive pressure locking technique. Before each infusion, the study nurses will mechanically wipe and sterilize the infusion connector. Catheter function will be assessed by flushing the catheters and aspirating for blood return. After seeing the blood return, the catheter will be flushed using short-interval pulsatile flushing (1 ml each time), for a total of 10 ml [22]. At the end of the infusion, prefilled saline syringes will be used to flush each lumen (even if only one lumen is used) via pulsatile flushing and the positive pressure technique [24].

The study will continue for 7 days unless there is catheter occlusion or catheter removal. During the 7 days, the study nurses will identify catheter occlusion by scoping the CINAS, observing the infusion status, and identifying the occlusion alarm. Once catheter occlusion occurs, the patients reach the end of the study, and the management of the blocked catheter will be referred to the physician and nurse. The end of the trial also includes a 2-day observation period, which will monitor the occurrence of catheter-related bloodstream infection (CRBSI), primarily through temperature monitoring.

Throughout the trial, the study team will fully respect the patient’s wishes, and the patients will have the right to withdraw from the trial. In addition, if a patient has no observed occlusion during the trial period and removes the CVC for other reasons, then the patient will be considered to have dropped out.

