**Table 1 Tab1:**
[figure not shown]
The Catheter Injection and Aspiration (CINAS) [25]

The secondary outcomes of this study include the 3-day catheter occlusion rate, which is also assessed by scoping CINAS, nurse satisfaction, and cost-effectiveness. Nurse satisfaction is defined as nurses’ attitudes towards these two different methods of flushing catheters. This outcome will be assessed by scoping a 5-point Likert scale (1 = Very dissatisfied, 2 = Dissatisfied, 3 = Unsure, 4 = Satisfied, 5 = Very satisfied). Cost-effectiveness will be assessed by calculating related medical expenses and nursing time and analysing the effect of the two methods.

The safety outcomes of this study are adverse event rates and intravenous therapy-related complications. The adverse events include unplanned removal, unplanned thrombolysis, and elastic pump failure. All these adverse events are defined as follows:

(I)Unplanned removal: intubation accidental dislodgement or removal of the catheter by the patient without the consent of the health care provider. This removal may also be the result of improper handling by the health care provider.(II)Unplanned thrombolysis: a thrombotic occlusion of the patient’s CVC and the CVC needs to be recanalized with a thrombolytic drug such as a fibrinogen activator.(III)Elastic pump failure: elastic pump breakage.

Intravenous therapy-related complications include CRBSI, catheter-related thrombosis (CRT), catheter misplacement, extravasation, and phlebitis. The definitions of these metrics are shown below:

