(I)CRBSI: bacteraemia or fungemia in a patient with an intravascular catheter or within 48 h of removal of an intravascular catheter with manifestations of infection such as fever (38 °C), chills, or hypotension, with no clear source of infection other than the vascular catheter. Laboratory microbiology reveals positive peripheral venous blood cultures for bacteria or fungi or pathogenic bacteria of the same species with the same drug-sensitive results from the catheter segment and peripheral blood cultures.(II)CRT: a mural thrombus extending from the catheter into the lumen of a vessel, leading to partial or total catheter occlusion with clinical symptoms that was established by Doppler colour flow imaging.(III)Catheter misplacement: the position of the catheter tip changes.(IV)Extravasation: fluid or drug extravasation.(V)Phlebitis: this includes chemical phlebitis, mechanical phlebitis, and infectious phlebitis. Clinical signs and symptoms include pain, pressure, erythema, and erythema. Grades will be assessed according to the phlebitis scale in the INS guidelines [22].

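### The plan does not say whether observation continues after an early occlusion or removal, so later safety and cost data are not secured and safety follow-up is modestly shorter in the arm with more occlusions

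*Protocol article*

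**What the plan says.** All references are to the Protocol article.

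- **Abstract, Method:** "Patients will be followed up until 9 days after CVC insertion, catheter occlusion, or catheter removal".
- **Intervention description {11a}:** "The study will continue for 7 days unless there is catheter occlusion or catheter removal". At occlusion, "the patients reach the end of the study, and the management of the blocked catheter will be referred to the physician and nurse". The section then continues: "The end of the trial also includes a 2-day observation period, which will monitor the occurrence of catheter-related bloodstream infection (CRBSI"), mainly by temperature. It does not say from which event the 2 days are counted.
- **Outcomes {12}:** CRBSI counts while the catheter is in place or "within 48 h of removal of an intravascular catheter". Unplanned thrombolysis means a thrombotic occlusion where "the CVC needs to be recanalized with a thrombolytic drug". CRT is defined through partial or total occlusion with symptoms, established by Doppler imaging. "Cost-effectiveness will be assessed by calculating related medical expenses and nursing time", set against the effect of the two methods.
- **Participant timeline {13}, Table 2:** vital signs, complications and adverse events are scheduled in Days 1-7 and again in Days 8-9. Medication, consumables and operation time are scheduled in Days 1-7 only.
- **Statistical methods {20a}:** count outcomes are compared by chi-square or Fisher's exact test.

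**The concern.** Occlusion is both the primary outcome and an event that ends a patient's time in the study. Several other outcomes arise at or after that event: thrombolysis is a treatment for it, CRT confirmation may follow it, and the cost of dealing with it comes afterwards. The Background {6a} itself names higher health care cost as a consequence of blockage. If centres follow the Abstract, these items may go unrecorded. If they follow the 2-day sentence in {11a}, some will be recorded. Fourteen centres could read the text differently.

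The plan also expects occlusion to be more frequent in the control arm. Ending observation there gives that arm less time in which infection or thrombosis can be seen, and the planned tests of proportions do not allow for this. Both effects would work against the test technique. Its daily pumps are recorded as consumables while avoided occlusion management is not secured on the cost side, and control-arm safety events are observed for a shorter time.

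**Working it through.** **1. The plan's own figure.** Sample size {14} assumes 25% occlusion in control and 10% in test, one-sided alpha 0.025, power 80% and 20% dropout. The pooled-variance formula for two proportions gives 100 per arm, and 100 / 0.8 = 125, as stated. The printed unpooled formula with margin 0 gives 7.849 × (0.1875 + 0.09) / 0.15² = 96.8, so 97, and 97 / 0.8 rounds up to 122. The stated 125 is reproduced, and the two rates are used below.

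**2. Patients affected.** Expected occlusions per 125 randomised: control 0.25 × 125 = 31.25, test 0.10 × 125 = 12.5.

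**3. Safety follow-up per patient.** Assume occlusions are spread evenly over 7 days (mean 3.5 days), no other early end, and everyone else followed to Day 9. With occlusion probability p:

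- observation stops at occlusion: mean = 9 − p × (9 − 3.5) = 9 − 5.5p
- 2 more days after occlusion: mean = 9 − p × (9 − 5.5) = 9 − 3.5p

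| Reading of the text | Control (25%) | Test (10%) | Control shortfall |
|---|---|---|---|
| Stops at occlusion | 7.63 days | 8.45 days | 9.8% |
| 2 days follow occlusion | 8.13 days | 8.65 days | 6.1% |

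**4. Sensitivity.**

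- *Constant hazard instead of even timing:* 7.58 vs 8.44 days if observation stops at occlusion, a test-to-control ratio of 1.11.
- *Control rate 38%, the upper end of the range in {14}:* under constant hazard, 6.80 vs 8.44 days, ratio 1.24.
- *Equal 20% removal or dropout in both arms:* the 25% vs 10% ratio stays at 1.11.
- *Timing, stopping at occlusion:* the scheduled patency checks are on Days 3 and 7. If every occlusion were found on Day 3, the means are 9 − 6p, or 7.5 vs 8.4 days (10.7% less in control). If every one were found on Day 7, they are 9 − 2p, or 8.5 vs 8.8 days (3.4% less).

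**5. What each passage secures after an early occlusion or removal.**

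- *CRBSI:* the definition needs 48 h after removal. The Abstract gives none, and {11a} gives 2 days but does not tie them to an early end. Table 2 places them at Days 8-9.
- *Thrombolysis and CRT:* complications and adverse events have Day 8-9 entries in Table 2, but {11a} says the occluded patient has reached the end of the study.
- *Occlusion-management cost:* consumables and operation time stop at Day 7, and no passage extends them past an occlusion.

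**The case against.** A reader might infer that CRBSI after removal, and thrombolysis, cannot be captured at all. The documents do not support that. The 2-day observation in {11a} matches the 48 h in the CRBSI definition, and Table 2 schedules complications and adverse events on Days 8-9. Adverse events reporting {22} names occlusion as an expected complication, has nurses monitor complications daily, and asks them to report the situation and outcome of an adverse event. That is a plausible route for thrombolysis to be recorded. This part of the objection stands: capture is unsecured, not impossible.

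A reader might also infer that cost-effectiveness gives the test technique no credit for avoided occlusions. Outcomes {12} sets costs against the effect of the two methods, so avoided occlusions may be credited as effect. The phrase on medical expenses is not expressly limited to the rows of Table 2, and cost components are often left to a fuller document. What remains is that no passage provides for recording cost after an occlusion.

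A third inference would be that the crude safety proportions are not comparable. The article gives no expected CRBSI or CRT rate, so the absolute effect of a 6% to 10% gap in follow-up cannot be stated. The 20% dropout allowance applies to both arms and adds no imbalance. The gap is real but modest.

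None of this settles whether the 2 days follow an early end, and an analysis plan cannot recover data that were not collected.

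**Conclusion.** The point holds as an unresolved inconsistency with a modest consequence for safety and cost outcomes. The Abstract and {11a} end the study for a patient at occlusion, and the 2-day CRBSI observation is not tied to an early end. Recording of thrombolysis, CRT confirmation and management cost after an occlusion is therefore not assured for about 31 control and 12 to 13 test patients per 125.

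Under even timing and the planned rates, control safety follow-up is about 10% shorter if observation stops at occlusion, or about 6% shorter if the 2 days apply. At a 38% control rate the test-to-control ratio of follow-up could reach about 1.24, assuming constant hazard and no observation after occlusion. These figures rest on design rates and assumed timing, not on observed data.

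The primary outcome is not biased by this rule, because occlusion is itself the stopping event, and the sample size is unaffected.

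**What to change.** Reconcile the Abstract, {11a}, the CRBSI definition in {12} and Table 2 so that they state one rule: occlusion or removal ends the allocated intervention but not observation. For every randomised patient still in hospital, record CRBSI, CRT, thrombolysis, and occlusion-related consumables, expenses and nursing time from charts to a fixed Day 9. Extend the consumables and operation-time rows of Table 2 to match.

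A fixed Day 9 covers 48 h after any removal in Days 1-7 (7 + 2 = 9) and removes the imbalance that comes from stopping at occlusion. An end date tied to catheter removal would be open-ended, because {18b} selects patients expected to keep the catheter for more than 8 days. Discharge or transfer to another hospital would still end tracking, as {18b} says, and that date should be recorded. Report infection and thrombosis per catheter-day beside the proportions.

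The cost is revised wording and slightly more data entry, with no added patient procedure. Trial status gives data collection as complete on July 31, 2023. If it is closed, retrieve these items from charts where possible; otherwise disclose the truncation and limit the safety and cost-effectiveness conclusions accordingly.

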**Discussion:**

We expect that the trial will generate findings that can provide an evidence-based basis for the improvement and optimization of clinical catheter flushing techniques.

**Trial registration:**

Chinese Clinical Trial Registry, ChiCTR2200064007. Registered on 23 September 2022. https://www.chictr.org.cn/showproj.html?proj=177311.

**Supplementary Information:**

The online version contains supplementary material available at 10.1186/s13063-024-08141-6.

## Introduction

### Background and rationale {6a}

Maintaining unobstructed venous access is of great clinical importance [1, 2]. The central venous catheter is widely used in clinical practice, with single-lumen, double-lumen, and multi-lumen, and can be used for monitoring hemodynamic, infusion therapy, blood transfusion, chemotherapy, and parenteral nutrition [3, 4]. The complications associated with central venous catheters can reach 40% [5], and common complications include occlusion, infection, and catheter dislodgement [6], with occlusion occurring in 25% to 38% of cases [7]. Blockage of a catheter can affect the patient’s treatment [8] or, worse, can threaten the patient’s life and increase health care costs [9].

The central venous catheter occlusion factors can be divided into intrinsic and extrinsic factors. Intrinsic factors, such as advanced age, female sex, hypercoagulable blood, and disease, are related to the patients themselves and can lead to an increased probability of catheter occlusion [10]. Extrinsic factors include the catheter placement site, number of punctures, catheter folding, improper flushing, and nature of the infused drug [11, 12]. Improper flushing, for example, failure to flush the lumen in a timely manner, failure to use the correct locking solution, or failure to use the correct flushing technique, can increase the probability of catheter occlusion [13, 14]. In addition, infusion of specific drugs can also lead to occlusion; for example, infusion of drugs that are hypertonic, too high, or too low in pH can easily lead to changes in plasma osmolality, thrombus formation, catheter tip occlusion, or haemagglutination occlusion [15].

Keep vein open (KVO) refers to the practice of keeping a vein open with a small amount of intravenous solution [16]. Previous studies have focused mainly on comparing the effects of intermittent flushing and continuous infusion on peripheral intravenous catheters and neonates [17, 18]. However, none of these studies have offered a comparison in the adult population. In this study, we will ameliorate KVO infusion and use it in the adult population. We will use an elastic pump to run continuous infusion rather than gravity infusion. This kind of elastic pump contains 50 ml of 0.9% sodium chloride solution, and KVO infusion can be applied at a rate of 2 ml/h. KVO infusion was used between doses of intermittent medication in previous studies. In this study, participants will receive a whole-day KVO infusion, regardless of whether the participants are on intermittent medication.

Studies [19–21] have shown that the use of an elastic pump achieves the same results as heparin locking in general surgery patients with discontinuous infusions using single-lumen central venous catheters and in the maintenance of peripheral venous catheters, ensuring 100% catheter patency. The elastic pump infusion technique is designed to maintain the infusion pressure at 55 kPa, which is much higher than the human central venous pressure (0.5 ~ 1.2 kPa), by adopting the clinical micropump and infusion pump precision infusion principal technique and the built-in flow limiter, which can achieve continuous dynamic infusion and maintain catheter patency.

It is worthwhile to further investigate what kind of flushing technique can better ensure the patency of anterior-open multilumen central venous catheters (CVCs), which are widely used in continuous infusions, to ensure the safety of patient treatment and ease of movement. We completed a pretest with a sample of 20 patients to test the effectiveness of the KVO flushing technique for maintaining the patency of dual-lumen CVCs. The experimental results showed that no catheter occlusion occurred in the test group, while two cases of catheter occlusion occurred in the control group. Therefore, our team plans to expand the sample size and design a multicentre clinical control trial to test the effectiveness of this technique.

### Objectives {7}

The primary objective is to determine whether flushing a catheter under KVO infusion is superior to flushing a catheter under prefilled saline syringes. The secondary objectives are to establish and optimize the flushing and locking technique for CVC and establish standardized operating procedures (SOPs) for this technique.

### Trial design {8}

This is a multicentre**,** randomized controlled, parallel-group, open-label, superiority clinical study with two groups: (1) patients in the test group will receive KVO infusion to maintain CVC patency with elastic pumps (GEMTIER MEDICAL, 50 ml, 2 ml/h) and (2) patients in the control group will receive routine care.

After providing informed consent from patients, they will be assigned to either the test group (with continuous flushing of the CVC under KVO infusion) or the control group (with intermittent flushing of the CVC with prefilled saline syringes) at a 1:1 ratio (Fig. 1).

**Fig. 1 Fig1:**
[figure not shown]
Flowchart of the study

## Methods: Participants, interventions, and outcomes

### Study setting {9}

The 14 centres included in this study are located in Jiangsu Province, Anhui Province, and Hunan Province, China. The departments involved in this study include the intensive care unit (ICU), surgical ward, and oncology ward.

#### Eligibility criteria {10}

The inclusion criteria for patients will be as follows: (1) hospitalized using an anterior-opening double-lumen CVC; (2) aged 14 to 80 years; (3) newly placed CVC within 24 h; (4) had a normal catheter function (catheter injection and aspiration CINAS judged as IN1AS1); (5) voluntarily participated in this research; (6) had CVC placed through the internal jugular vein or subclavian vein; and (7) had a daily continuous infusion time ≥ 16 h. The exclusion criteria for patients will be as follows: (1) had existing catheter-related complications; (2) uses drugs incompatible with 0.9% sodium chloride solution; (3) uses drugs that cannot tolerate stopping infusion for flushing and locking the catheter; and (4) were locked with other locking solutions.

#### Who will take informed consent? {26a}

Informed consent will be obtained from the sub-investigators (SIs). During the trial screening period, the SIs will be responsible for subject screening. Patients in the ward who are possibly eligible for enrolment will be selected and informed about this trial in detail. If the patient agrees to participate in the study, then the patient will need to sign an informed consent form.

#### Additional consent provisions for collection and use of participant data and biological specimens {26b}

This trial does not involve collecting biological specimens for storage.

### Interventions

#### Explanation for the choice of comparators {6b}

The INS guidelines recommend the use of the pulsatile flushing technique [22]. The pulsatile flushing technique is widely used in clinical practice, and choosing this technique as a control group can improve the detection efficacy of the test group technique.

#### Intervention description {11a}

The placement and maintenance of CVCs are carried out by trained and qualified professionals. Disinfectants that meet Chinese regulations [23] are selected for puncture and maintenance, creating a maximum sterile barrier and using a uniform catheter placement process. We previously standardized the type of CVC (FORNIA, CVC-2 7F 20) to be applied in this study to reduce interference. In addition to the flushing technique, other care measures for the catheter will be carried out according to the same standard, including using the same infusion connector (BD Luer-Lok™ 394605), changing the dressings once a week**,** and changing the infusion once a day; in special cases, the frequency of replacement will increase.

Depending on the grouping, patients in the test group will undergo KVO infusion using an elastic pump containing 50 ml of 0.9% sodium chloride solution, which maintains a constant pressure (55 kPa) and a steady infusion rate (2 ml/h). Before daily infusion, the study nurses will mechanically wipe and disinfect the infusion connector, connect the stopcocks according to the infusion demand, connect the elastic pump to the female opposite port of the endmost stopcocks, connect the medication pathways to the female side ports, adjust the stopcocks handle for infusion and flushing, and fix the elastic pump appropriately to observe the liquid in the elastic pump and pumping situation at regular intervals. At the end of the infusion, the stopcock handle will be adjusted to close the medication pathway, and the pumping of the elastic pump will be continued. The study nurses will change the pumps once a day. The elastic pump pumping valve will be closed, the elastic pumps will be separated from the stopcocks or catheters, and the stopcocks will be mechanically disinfected. Two new elastic pumps will then be connected, the handle will be adjusted to continue pumping, and the elastic pumps will be properly fixed to ensure that it does not interfere with patient activities.

In the control group, prefilled saline syringes containing 10 ml of 0.9% sodium chloride injection will be used to flush and lock the catheter via pulsatile flushing and the positive pressure locking technique. Before each infusion, the study nurses will mechanically wipe and sterilize the infusion connector. Catheter function will be assessed by flushing the catheters and aspirating for blood return. After seeing the blood return, the catheter will be flushed using short-interval pulsatile flushing (1 ml each time), for a total of 10 ml [22]. At the end of the infusion, prefilled saline syringes will be used to flush each lumen (even if only one lumen is used) via pulsatile flushing and the positive pressure technique [24].

The study will continue for 7 days unless there is catheter occlusion or catheter removal. During the 7 days, the study nurses will identify catheter occlusion by scoping the CINAS, observing the infusion status, and identifying the occlusion alarm. Once catheter occlusion occurs, the patients reach the end of the study, and the management of the blocked catheter will be referred to the physician and nurse. The end of the trial also includes a 2-day observation period, which will monitor the occurrence of catheter-related bloodstream infection (CRBSI), primarily through temperature monitoring.

Throughout the trial, the study team will fully respect the patient’s wishes, and the patients will have the right to withdraw from the trial. In addition, if a patient has no observed occlusion during the trial period and removes the CVC for other reasons, then the patient will be considered to have dropped out.

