#### Relevant concomitant care permitted or prohibited during the trial {11d}

This is a randomized controlled study, and contamination between the two groups should be avoided. Therefore, pulsative flushing is prohibited for the test group.

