#### Methods in analysis to handle protocol non-adherence and any statistical methods to handle missing data {20c}

For possible missing data during the study, the analysis will be carried forward for missing primary outcomes, and the specific carryover method is described in “Statistical methods for primary and secondary outcomes {20a}” section. Catheter occlusion is defined as a partial or complete occlusion of an intravascular catheter, resulting in blocked or restricted infusion of fluid or medication. For subjects who failed to complete the primary outcome evaluation, the method of worst-case imputation will be used to handle missing values. That is, if subjects withdraw early or for any other reason and the primary outcome is missing, the decision of whether or not catheter occlusion occurred will be treated as occlusion.

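### The routine flush-and-aspirate check before each infusion is written for the control arm only, so transient or aspiration-only occlusions can be found more often there and, if scored, would favour KVO

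*Protocol article*

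**What the plan says.** **Control arm** (Intervention description {11a}). The pre-infusion procedure opens with "Before each infusion, the study nurses will mechanically wipe and sterilize the infusion connector" and continues with "Catheter function will be assessed by flushing the catheters and aspirating for blood return". Each lumen is also hand-flushed after the infusion.

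**Test arm** (same section). The daily procedure starts "Before daily infusion, the study nurses will mechanically wipe and disinfect the infusion connector, connect the stopcocks according to the infusion demand". The routine observation is to "fix the elastic pump appropriately to observe the liquid in the elastic pump and pumping situation at regular intervals", and the pumps are changed daily. No aspiration or hand flush is described. The section on concomitant care {11d} adds: "Therefore, pulsative flushing is prohibited for the test group".

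**Both arms.** The abstract says "All the catheters will be checked for patency by scoping Catheter Injection and Aspiration (CINAS) Classification on Days 3 and 7". Section {11a} says, without naming an arm, that during the 7 days the nurses "identify catheter occlusion by scoping the CINAS, observing the infusion status, and identifying the occlusion alarm". Section {22} lists occlusion among the expected complications and has nurses monitor complications daily.

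**What counts.** The primary outcome adds partial to complete occlusions {20a}. Outcomes {12} assesses occlusion by CINAS, which grades both injection and aspiration. Section {20c} defines it as partial or complete occlusion "resulting in blocked or restricted infusion of fluid or medication". An occlusion ends participation {11a}. Only the data analysts are blinded {17a}.

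**The concern.** If aspiration is tried more often in one arm, impaired aspiration can be found more often there. A 2 ml/h infusion that is still running, with no alarm, need not reveal that blood cannot be withdrawn. A partial occlusion of that kind, present on one day and gone by the next CINAS, has a route to being recorded in control and no equivalent routine route in the test arm. One such finding can settle a control patient's primary outcome, because the outcome is binary and an occlusion closes follow-up.

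The direction favours the test arm, and the people who look for and record the event know the allocation. At stake is whether a lower recorded rate under KVO reflects patency or partly reflects how often someone tried to aspirate.

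**Working it through.** **1. The plan's own figure.** With 25% vs 10%, one-sided α = 0.025 and power 0.80, the pooled-variance formula gives 100 per arm, and 100 / (1 − 0.20) = 125. The stated 125 is reproduced, so this point does not touch the sample size calculation.

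**2. Routes to an event, side by side.**

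| Route | Control | Test |
|---|---|---|
| CINAS on Days 3 and 7 | yes | yes |
| Infusion status, occlusion alarm | yes | yes |
| Daily complication monitoring | yes | yes |
| Observation of the elastic pump | not applicable | yes |
| Flush and aspiration before each infusion | yes | not described |

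Only the last row adds routine aspiration, and it is in control alone.

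**3. Illustration with no true effect.** Assumptions, none of them given in the documents:
- persistent occlusion of 10% in both arms;
- probability q per check of a transient aspiration difficulty, independent between checks;
- every such finding is scored as a primary event.

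The test arm has k = 2 checks. Control has k = 7 (one per day, coinciding with CINAS on Days 3 and 7) or k = 9 (one per day plus two separate CINAS). One check per day is inferred from the daily change of infusion in {11a}.

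Recorded rate = 1 − 0.90 × (1 − q)^k. For q = 1%:
- test: 1 − 0.90 × 0.99² = 11.8%;
- control, k = 7: 1 − 0.90 × 0.99⁷ = 16.1%;
- control, k = 9: 1 − 0.90 × 0.99⁹ = 17.8%.

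If the planned 20% dropout is imputed as occlusion in both arms {20c}, each rate becomes 0.20 + 0.80 × rate. For q = 1% that is 29.4% (test) against 32.9% or 34.2% (control).

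The decision rule is the one in {20a}: the upper 95% limit for test minus control lies below 0. I used the Wald interval and enumerated the two binomials exactly at 125 per arm.

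| q per check | Test rate | Control rate (k = 7; 9) | False superiority, no dropout (k = 7; 9) | False superiority, 20% imputed (k = 7; 9) |
|---|---|---|---|---|
| 0.5% | 10.9% | 13.1%; 14.0% | 8.2%; 11.6% | 5.0%; 6.4% |
| 1% | 11.8% | 16.1%; 17.8% | 17.2%; 27.5% | 8.7%; 12.9% |
| 2% | 13.6% | 21.9%; 25.0% | 41.5%; 64.1% | 20.4%; 33.7% |

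With q = 0 the rule rejects in 2.7% of trials without dropout and in 2.6% with 20% imputed, close to the nominal 2.5%. The rest is due to the unequal number of checks.

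**4. Which definition applies.** Under {12}, difficult or impossible aspiration is part of the instrument that assesses occlusion. Under {20c}, the event needs impaired infusion. Loss of blood return alone can therefore be an event under the first and not under the second. It is also the sign that control is checked for more often.

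**The case against.** A reader might infer that the test arm is examined only on Days 3 and 7. The documents do not support that. Infusion status, the alarm and daily complication monitoring are written without naming an arm, the pumps are observed and changed, and Table 2 places patency assessment across Days 1 to 7. What is unequal is routine aspiration and hand flushing, not surveillance as a whole. Even if Table 2 meant a daily CINAS for everyone, the control pre-infusion check would still be additional.

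A reader might also infer that more control occlusions are bound to be detected. That does not follow either. A persistent occlusion meets the common CINAS in both arms. The pre-infusion aspiration is described as part of the flushing procedure, and no section says that failing it is scored as a primary event. If only CINAS results count, or if the {20c} definition governs, most of the mechanism disappears.

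The magnitude rests on an assumed per-check rate, and imputing dropouts as occlusion in both arms roughly halves the larger figures. All of this stands and limits the point. It does not remove it. The protocol leaves the scoring open, writes the extra check for one arm only and has unblinded nurses decide.

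**Conclusion.** The point holds in a limited form. As written, the plan gives control catheters a routine aspiration check that test catheters lack. Transient or aspiration-only partial occlusions can then be recorded more often in control, which favours KVO if they are scored. The direction is clear, but the size is unknown. Under the stated assumptions, false superiority ranges from about 5% (0.5% per check, 7 control checks, dropouts imputed) to about 64% (2% per check, 9 control checks, no dropout). These figures show sensitivity to the assumption and do not estimate the bias in this trial.

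It would go too far to say that the effect could never be separated from a treatment effect. If detection route, CINAS codes and dates are recorded, an analysis on the common assessments can show how much depends on the extra check. This is a cheap improvement to the outcome definition.

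**What to change.** 1. Define the primary event by one rule for both arms: an abnormal CINAS at the common scheduled assessments (Day 3, Day 7), or an infusion stoppage or occlusion alarm confirmed by a full CINAS.
2. Record control-arm pre-infusion findings with their detection route, but do not count them on their own as primary events. Such a finding should not by itself close outcome follow-up. Otherwise no later CINAS exists, and the worst-case imputation in {20c} turns the finding back into an event.
3. Reconcile {12} and {20c}, stating whether loss of blood return alone is an occlusion.
4. Add a sensitivity analysis that uses only the scheduled Day 3 and Day 7 CINAS results. One restricted to impaired injection would not equalise detection, because control lumens are also hand-flushed more often.
5. Also report the primary result with the pre-infusion findings counted.

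The cost is wording, one CRF field and two extra analyses. The downside is that some control-arm events found between visits are counted later, or are lost if they resolve or are managed before the next CINAS. Step 5 shows how much this matters. The trial status section gives July 2023 as the end of data collection, so steps 1, 3, 4 and 5 can be applied only as far as CINAS codes, dates and the reason for ending participation were recorded.
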